### Recruitment {15}

Participants will be recruited at TOH through two potential recruitment streams. The first clinic sees Ontario workers who were infected by SARS-CoV-2 at their worksite, who have made a claim to the Ontario WSIB and are assessed by the OWN based at TOH. The second stream is any clinics within TOH which are seeing patients with Long COVID. These are either clinics specifically for people with Long COVID, for example within respirology, infectious diseases, or psychiatry. The anticipated flow of recruitment is outlined in Fig. 1 below.

**Fig. 1 Fig1:**
[figure not shown]
Patient flow

## Assignment of interventions: allocation

### Sequence generation {16a}

Randomization will be done remotely by the Ottawa Methods Centre (OMC) through an electronic randomization system. Participants will be randomized at enrollment by a delegated study staff member. As participants are created in the ECDS, they are automatically randomized. The delegated study staff member will be informed of the allocation at the time of randomization.

Allocation will be a 1:1 ratio into the treatment arms. Participants will be stratified by sex and duration of symptoms. The reasons for stratification by sex are that the mortality rate in males is higher than in females and that outcomes may be affected by gendered occupations [63–66]. We will stratify by the duration of symptoms into two groups: (1) those who at enrolment have had symptoms since the onset of their index illness for 12 to 23 weeks, and (2) those who have had symptoms at enrolment for 24 weeks or longer, which is consistent with the classification of Long COVID in the NICE guidelines. We are stratifying for duration of illness as this is one of the main determinants of outcomes.

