### Participant timeline {13}

Administration will occur as per the Time and Events Schedule in Table 5. Clinical visits will occur as needed and will be determined during the initial assessment. Clinical visits are not outlined in the time and event schedule as these are a part of routine care. Self-report measures will be completed at home prior to each study visit using the study Electronic Data Capture System (EDCS). Participants will be able to leave and return to the questionnaires whenever they need to complete them. It is anticipated the first and last visit will take approximately 45 min, while weeks 4 and 8 will take approximately 30 min. Participants will complete the WHODAS first and all responses are mandatory. All other self-report measures will be completed in a structured order.

**Table 5 Tab5:** Time and events schedule

Measures	Time to complete (minutes)	Administration	Baseline	Week 4	Week 8	Week 12
WHO Post COVID CRF Module 1	Variable	Chart review	**X**			
WHO Post COVID CRF Module 2	Variable	Chart review	**X**			**X**
WHO Post COVID CRF Module 3	Variable	Chart review	**X**			**X**
Demographics	<5	Self-report	**X**			
ACE-Q	5	Self-report	**X**			
Injustice Experience Questionnaire (IEQ-SF)	<5	Self-report	**X**			
WHODAS	5	Self-report	**X**	**X**	**X**	**X**
PHQ-9	<5	Self-report	**X**	**X**	**X**	**X**
GAD-7	<5	Self-report	**X**	**X**	**X**	**X**
PCL-5	5	Self-report	**X**	**X**	**X**	**X**
EQ-5D-5L	<5	Self-report	**X**	**X**	**X**	**X**
AUDIT	<5	Self-report	**X**			**X**
ASSIST	5-10	Interview	**X**			**X**
Fatigue Severity Scale	<5	Self-report	**X**	**X**	**X**	**X**
PSQI	5	Self-report	**X**	**X**	**X**	**X**
Warwick-Edinburgh Mental Wellbeing Scale (WEMWBS)	5	Self-report	**X**			**X**
Pain Numeric Rating Scale	<5	Self-report	**X**	**X**	**X**	**X**
MRC Dyspnoea Scale	<5	Self-report	**X**	**X**	**X**	**X**
Cognition (Trailmaking, Hopkins Verbal Learning, Digit Span, Phonemic/Semantic Verbal Fluency)	30	Interview	**X**			**X**
Qualitative Interview (Optional)	30	Interview				**X**

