### Implementation {16c}

Once participants have consented and completed screening determining eligibility, they will be registered in the ECDS and randomization system by the delegated research staff member. Once the participant is registered, the system will automatically allocate the participant to the intervention.

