## Data collection and management

### Plans for assessment and collection of outcomes {18a}

All self-reported outcome measures will be administered via the EDCS for all study visits. Interview measures, when done remotely, will be completed using a videoconferencing platform. Information from the WHO Post-COVID Assessment CRF will be entered by delegated study staff into the EDCS.

Cognitive assessments will be administered by a trained research staff member. The delegated study staff member will receive direct training from an experienced Psychologist, including rehearsal and independent evaluation, prior to administration with participants.

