### Confidentiality {27}

All records will automatically be assigned a unique Participant ID during randomization. The Participant ID will be recorded on a master linking log. The master linking log will be password-protected and stored with limited access as per institutional policy. The Participant ID will appear on all documentation included in a participant’s research chart, including study forms and correspondence, in order to maintain participant confidentiality. All correspondence with participants will be de-identified, removing names and other potentially identifying information, prior to being included in the study chart. Some documentation will remain identifiable including the Informed Consent Form, the Participant Information Form, and the Emergency Contact Form. These will not be stored with documentation identified with a Participant ID. Hard copy documentation will be stored in a double locked area (e.g., locked cabinet and secure office space). Study documents will be password-protected, and a log is kept separately from the documents so that access to the files is not lost in the event of staff turnover or during the archiving period. Electronic documents will not be stored on mobile devices (such as a USB or directly on a laptop).

Documents requiring de-identification must use an approved method. Electronic documents must be redacted so that the information removed cannot be recovered at a later time utilizing a tool such as Adobe Pro “Redact” feature, permanently obscuring the data. Hardcopy documentation will be redacted using only a “china marker,” which completely obscures the data. Sharpie, pen, and other writing tools are not permitted as they do not permanently obscure/destroy the data.

Participants’ study information will not be released unless a delegated study staff member obtains written permission from the participant or where required by law. Participants will not be identified in study presentations or publications. Once all study activities are complete, all study records and data exports will be archived at a secure storage facility for a period of 10 years, as per the applicable Network of Networks (N2) Standard Operating Procedure (SOP) and GCP regulations. The 10-year period will begin from the date the last informed consent form is signed.

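### As written, creating the data-capture record is the act of randomisation, so in this open-label trial baseline self-reports other than the qualifying WHODAS fall after allocation

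*Protocol article*

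**What the plan says.** Sequence generation {16a} ties allocation to record creation: "As participants are created in the ECDS, they are automatically randomized". It adds: "The delegated study staff member will be informed of the allocation at the time of randomization". Implementation {16c} gives the order: "Once participants have consented and completed screening determining eligibility, they will be registered in the ECDS and randomization system", and then "Once the participant is registered, the system will automatically allocate the participant to the intervention". Confidentiality {27} places the identifier at the same point: "All records will automatically be assigned a unique Participant ID during randomization".

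Plans for assessment and collection of outcomes {18a} states: "All self-reported outcome measures will be administered via the EDCS for all study visits". Participant timeline {13} has participants fill in the self-reports at home in the EDCS before each study visit, and Table 5 includes a baseline column for all of them. Table 5 also schedules the cognitive battery and ASSIST at baseline, as interviews; section 18a has research staff administer the cognitive tests.

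Trial design {8} makes the trial open label for patients and clinicians. Table 1 under Eligibility criteria {10} requires a self-reported WHODAS sum score of at least 15.

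**The concern.** A baseline value protects a comparison only if allocation could not have influenced it. Here the system that holds the baseline questionnaires opens a record only by randomising the person, and nothing requires the baseline measures to be finished first. In an open-label trial with mainly self-reported outcomes, someone who knows the arm may answer differently out of hope or disappointment, and an interviewer who knows it may test or score differently.

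Two analyses use baseline directly. Statistical methods {20a} models linear change in the primary outcome over four time points, so baseline WHODAS is itself one of the modelled responses. The economic evaluation under Outcomes {12} derives QALYs from the area under the EQ-5D-5L utility curve, which starts at baseline. A difference between arms created at baseline by knowledge of the arm would enter both, and no later analysis could separate it from a treatment effect.

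**Working it through.** **Order of events.** The protocol gives no figure for this point, so the first check sets the sections side by side. Sections 16a and 16c write ECDS; the abbreviation list has only EDCS, and I read them as one system.

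1. Consent and eligibility screening come first (16c). Screening includes WHODAS of at least 15 (Table 1).
2. Staff register the participant in the data-capture and randomisation system (16c).
3. Registration randomises automatically, and staff are told the arm (16a, 16c). The Participant ID is assigned now (27).
4. Self-reports are completed in the data-capture system at all visits (13, 18a). No record or identifier is described before step 3, so baseline self-reports belong after it.
5. The cognitive tests and ASSIST have no stated place before step 2.

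Intervention description {11a} is compatible with this order: it offers the clinician assessment to people already randomised to the control arm, and it calls the initial consultation the baseline visit.

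**Which baselines are affected.** A WHODAS score must exist at step 1. The other self-reports scheduled at baseline in Table 5 (PHQ-9, GAD-7, PCL-5, EQ-5D-5L, FSS, PSQI and others) are not entry criteria and fall at step 4. For WHODAS, two readings remain: the screening score is the baseline, or WHODAS is repeated in the system at step 4 and that score is the baseline.

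**Size if WHODAS is repeated at step 4.**

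Inputs from the protocol:
- Sample size {14}: mean 17, SD 4, target a 10% change, so 0.10 × 17 = 1.7 points.
- Table 5: visits at weeks 0, 4, 8 and 12, that is, four equally spaced points.

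Assumption, not in the protocol: knowing the arm shifts the baseline mean of one arm by d = 0.5 to 1 point (0.5/4 = 0.125 SD to 1/4 = 0.25 SD), with later visits unaffected.

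Ordinary linear trend, complete data:
- Centred times are −1.5, −0.5, 0.5 and 1.5. Their sum of squares is 2.25 + 0.25 + 0.25 + 2.25 = 5.
- Change in slope per interval = −1.5 × d / 5 = −0.3d.
- Over three intervals, change in the fitted 12-week change = −0.9d.

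| d (points) | Shift in fitted 12-week change, absolute | Share of 1.7 |
|---|---|---|
| 0.5 | 0.45 | 26% |
| 1.0 | 0.90 | 53% |

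The minus sign means that an arm whose baseline is pushed up (worse) appears to improve more. The bias can favour either arm.

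**QALYs.** With the trapezoidal rule (assumed) over the same four visits, baseline carries half of the first 4-week interval: 2 of 12 weeks, or one sixth of the weight. The protocol gives no basis for the size of a utility shift, so I give no QALY figure.

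**The case against.** The strongest objection concerns the primary outcome. Since a qualifying WHODAS precedes registration, its baseline may well be the screening score. In that case the primary analysis is protected and the 26% to 53% range does not apply. This stands: the documents do not establish that baseline WHODAS follows allocation. They do leave the matter open, and a score taken before any record exists does not fit section 18a.

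A reader might infer that eligibility is checked after randomisation, with late failures becoming post-randomisation exclusions. The text does not support this. Section 16c puts completed eligibility screening before registration.

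A reader might also infer that participants know their arm when they fill in the baseline forms. The protocol says when staff learn it, not when participants do. Early knowledge is likely in an open-label trial, and nothing delays disclosure, but it is not stated. For the interviews, the exposed route is staff knowledge; the text neither says that the tester is the person who randomised nor describes the tester as blinded.

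The shift d is assumed. Section 20a also reports mean differences, and an unadjusted week-12 difference would not be touched by a baseline shift. The figures therefore apply only to the linear-change model.

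Finally, this is a condensed article and the patient-flow figure (Fig. 1) was not available to me. The full protocol or the figure may show a screening record or another order. That lowers certainty about actual practice, but sections 16a and 16c state an order rather than leave one out, and that wording would still need correcting.

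**Conclusion.** The concern holds in limited form. Followed as written, the protocol collects the baseline self-reports other than the qualifying WHODAS after allocation in an open-label trial, and it does not require the cognitive tests or ASSIST to precede allocation. This rests on reading ECDS as EDCS and on no earlier record existing, since none is described.

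For WHODAS the exposure is conditional. If the screening score is the baseline, there is none. If WHODAS is repeated after registration, the linear-change estimate moves by 0.9 times whatever shift occurs: 0.45 to 0.9 points for an assumed 0.5 to 1 point, against a 1.7-point target. That is an illustration of sensitivity, not an estimate of bias. The QALY analysis is exposed through baseline EQ-5D-5L under either reading.

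**What to change.** Separate record creation from randomisation in sections 16a and 16c, and state the order:

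1. After consent, create the record under a screening ID.
2. Complete and lock all baseline self-reports, the cognitive tests and ASSIST, and confirm eligibility.
3. Only then trigger randomisation and release the allocation to staff and participant.

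State that the pre-randomisation WHODAS is the baseline value for every analysis. Amend section 27 so that an identifier exists before allocation, and use one abbreviation for the system.

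The cost is a workflow setting, a few sentences of text and slightly later allocation for each participant. Trial status reports one participant enrolled at the time of writing, so a change at that point would affect almost no data. Baselines already collected after allocation cannot be repaired in the analysis.

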### Concealment mechanism {16b}

Not applicable. Since the interventions are assigned through random computer generation, allocations are not visible in advance, and no concealment is required.

### Implementation {16c}

Once participants have consented and completed screening determining eligibility, they will be registered in the ECDS and randomization system by the delegated research staff member. Once the participant is registered, the system will automatically allocate the participant to the intervention.

## Assignment of interventions: blinding

### Who will be blinded {17a}

Due to the nature of the intervention, a behavioral intervention where both patient and clinician must use an electronic platform, it is not possible to blind either group to their allocation. Data analysts and manuscript writers will be blind to the identity of the two groups which will be referred to as group A and group B. Once initial manuscript preparation is complete, the groups will be unblinded. We will also assess potential bias in recruitment during an interim analysis.

### Procedure for unblinding if needed {17b}

Not applicable—all participants and treating clinicians are unblinded to the intervention.

## Data collection and management

### Plans for assessment and collection of outcomes {18a}

All self-reported outcome measures will be administered via the EDCS for all study visits. Interview measures, when done remotely, will be completed using a videoconferencing platform. Information from the WHO Post-COVID Assessment CRF will be entered by delegated study staff into the EDCS.

Cognitive assessments will be administered by a trained research staff member. The delegated study staff member will receive direct training from an experienced Psychologist, including rehearsal and independent evaluation, prior to administration with participants.

### Plans to promote participant retention and complete follow-up {18b}

A major difficulty in all clinical research is ensuring participants attend their visits and stay enrolled in the study. Efforts will be made to minimize the time between being approached about the study and the baseline visit. We anticipate lost to follow-up to be no more than 20%. While there is currently no available literature on the lost to follow-up rates for Long COVID rehabilitation, the case management platform we are using has demonstrated significantly higher levels of retention in difficult to treat populations [24]. For those participants in the intervention arm, daily and weekly reminders will be programmed into the NexJ Connected Wellness platform to encourage regular use and increase connectedness with the platform, increasing retention.

We will implement an escalated approach if contact is lost with individuals between study visits. The appropriate response will be determined in collaboration with the Principal Investigator, particularly if there is a potential safety concern. If contact is made with the participant and they are no longer interested in participating, the delegated study staff member will make every effort to ascertain why they are withdrawing their consent. Participants will be sent the link to complete their self-report questionnaires at each time point unless they have withdrawn their consent for participation.

### Data management {19}

All study outcome data will be directly entered into an EDCS. Data will be automatically coded, and the code will be described using a data dictionary. Range checks will be included for illogical entries. Missing items will be flagged for self-entry; however, participants can bypass the warning. A delegated study staff member will follow-up on the missing entry to confirm if the question was missed or the participant is refusing to answer.

The EDCS is a username- and password-protected web-based system. All network, server security and privacy settings are regularly tested and comply with Health Canada recommendations and Good Clinical Practice (GCP) for secured data management services [67, 68]. The EDCS is hosted on a physical server, not in the cloud, that is located at TOH data center in a secure server room with access limited to authorized personnel behind lock doors. The web/database server is behind the TOH firewalls. The OHRI website is secured with the highest rating from Entrust SSL virtual test. The data transfer between the client and server is protected with Entrust SSL 256-bit encryption. All data transfers between the client computers/browsers and the server/database are encrypted via https.

### Confidentiality {27}

All records will automatically be assigned a unique Participant ID during randomization. The Participant ID will be recorded on a master linking log. The master linking log will be password-protected and stored with limited access as per institutional policy. The Participant ID will appear on all documentation included in a participant’s research chart, including study forms and correspondence, in order to maintain participant confidentiality. All correspondence with participants will be de-identified, removing names and other potentially identifying information, prior to being included in the study chart. Some documentation will remain identifiable including the Informed Consent Form, the Participant Information Form, and the Emergency Contact Form. These will not be stored with documentation identified with a Participant ID. Hard copy documentation will be stored in a double locked area (e.g., locked cabinet and secure office space). Study documents will be password-protected, and a log is kept separately from the documents so that access to the files is not lost in the event of staff turnover or during the archiving period. Electronic documents will not be stored on mobile devices (such as a USB or directly on a laptop).

Documents requiring de-identification must use an approved method. Electronic documents must be redacted so that the information removed cannot be recovered at a later time utilizing a tool such as Adobe Pro “Redact” feature, permanently obscuring the data. Hardcopy documentation will be redacted using only a “china marker,” which completely obscures the data. Sharpie, pen, and other writing tools are not permitted as they do not permanently obscure/destroy the data.

Participants’ study information will not be released unless a delegated study staff member obtains written permission from the participant or where required by law. Participants will not be identified in study presentations or publications. Once all study activities are complete, all study records and data exports will be archived at a secure storage facility for a period of 10 years, as per the applicable Network of Networks (N2) Standard Operating Procedure (SOP) and GCP regulations. The 10-year period will begin from the date the last informed consent form is signed.

### Plans for collection, laboratory evaluation, and storage of biological specimens for genetic or molecular analysis in this trial/future use {33}

Not applicable. There are currently no ancillary trials planned.

## Statistical methods

### Statistical methods for primary and secondary outcomes {20a}

The OMC will complete all data analyses. Baseline characteristics will be presented as means (or medians) with associated measures of variation for continuous variables, or frequencies and proportions for categorical data. We will use an intention-to-treat analysis based on all randomized participants. Additionally, we will analyze the primary and secondary outcomes based on the treatment received. Analyses will utilize a Gender-Based Analysis Plus (GBA+) focused Health Equity Impact Assessment (HEIA) [69] approach to examine how sex and gender interact with socioeconomic status, age, race/ethnicity, and rural/urban residence.

Analysis of primary and secondary outcomes will use relative risks and mean differences and be calculated and presented with 95% Confidence Intervals (CI). We will include subgroup analyses of participants by age, sex, and severity of Long COVID. The effects of group (control vs. experimental), Long COVID severity, and adverse childhood events on the linear change over time in the primary outcome (measured at 4 time points) will be analyzed using hierarchical regression. Bivariate associations between primary and secondary outcomes (and among secondary outcomes) measured at baseline and at the end of the study will be estimated with Pearson correlation coefficients (or Spearman correlation coefficients for non-parametric data).

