## Objectives {7}

### Primary objective

The primary objective of this trial is to determine if adding ECM with health coaching to usual care improves participant quality of life after 3 months for patients who present to hospital outpatient clinics experiencing Long COVID.

We hypothesize that adding ECM with health coaching to usual care will improve outcomes at 3 months compared to usual care alone.

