### Outcomes {12}

#### Primary outcome

To evaluate the primary outcome, improvement in quality of life, we will use the total sum score of the WHO Disability Assessment Scale (WHODAS 2.0) self-assessment. The WHODAS is a 36-item self-report questionnaire measuring health and disability from the previous 30 days across six domains of functioning: cognition, mobility, self-care, getting along, life activities, and participation. Responses are scored on a 5-point Likert scale: None [0], Mild [1], Moderate [2], Severe [3], and Extreme/Cannot Do [4] [32].

The WHODAS 2.0 has been validated using a cross-cultural approach in 19 countries and within 4 subgroups (general population, populations with physical problems, populations with mental or emotional problems, and populations with problems related to substance use). The WHODAS 2.0 showed excellent overall test-retest reliability (ICC=0.98) and internal consistency (Cronbach’s alpha = 0.98). The survey also showed good cross-cultural sensitivity and concurrent validity [32].

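### Two effect measures are given for the primary outcome, neither is named as decisive, and the only model specified targets a linear slope and not the 3-month difference

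*Protocol article*

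**What the plan says.** - **Objective.** The primary objective asks whether the intervention "improves participant quality of life after 3 months".
- **Outcome.** For this, the primary outcome section states: "we will use the total sum score of the WHO Disability Assessment Scale (WHODAS 2.0) self-assessment".
- **Population.** Section {20a} states: "We will use an intention-to-treat analysis based on all randomized participants". It then adds, as a further analysis, that "we will analyze the primary and secondary outcomes based on the treatment received".
- **First effect measure.** "Analysis of primary and secondary outcomes will use relative risks and mean differences", with 95% confidence intervals. The sentence names no visit and no covariates.
- **Second effect measure.** A model with three named terms (group, severity of Long COVID, childhood adversity), whose effects "on the linear change over time in the primary outcome (measured at 4 time points) will be analyzed using hierarchical regression".
- **Strata.** Sequence generation {16a}: "Participants will be stratified by sex and duration of symptoms". The same section justifies duration as a leading influence on outcome, and justifies sex by mortality differences and gendered occupations.
- **Timing.** The abstract gives 8 weeks of coaching. Table 5 places WHODAS at baseline and weeks 4, 8 and 12.
- **Sample size {14}.** Mean 17, SD 4, a 10% change, 80% power, alpha 0.05, 63 per group. No slope, repeated measure or baseline correlation is mentioned.

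**The concern.** A mean difference at a visit and a difference in linear slopes are different estimands. With one primary outcome and two undesignated analyses, the trial has two candidate primary results. If they disagree, the text does not settle which one stands.

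The model that the article does specify also fits its purpose poorly as a primary analysis:

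- It estimates a rate of change, whereas the objective is a difference at 3 months and the sample size rests on a difference in scores.
- It imposes a straight line from baseline to week 12, although treatment ends at week 8. A plateau or a waning effect after week 8 is plausible.
- It names two prognostic terms but omits both stratification factors. Leaving prognostic strata out of the model generally makes the standard error too large. The article gives no figures from which to size this.

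**Working it through.** **1. The plan's own figure.** Inputs from Sample size {14}: difference 0.10 × 17 = 1.7, SD 4, two-sided alpha 0.05 (sidedness is not stated), power 80%.

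n per group = 2 × (1.96 + 0.84)² × 4² / 1.7² = 86.9, so 87 and not 63. A one-sided test gives 69. The stated 63 corresponds to a 2.0-point difference. This is a separate defect, but it means that power for 1.7 points is already short before any choice of analysis.

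**2. Number analysed.** 152 × 0.8 = 121.6, about 61 per group.

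**3. Week-12 difference, with and without baseline adjustment.** With baseline to week-12 correlation ρ, the residual SD is 4 × √(1 − ρ²). The article does not give ρ, so 0.3 to 0.7 is an assumed range. Two-sided t-test power at 61 per group for 1.7 points:

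| ρ | Residual SD | Power |
|---|---|---|
| unadjusted | 4.00 | 64.4% |
| 0.3 | 3.82 | 68.5% |
| 0.5 | 3.46 | 76.7% |
| 0.6 | 3.20 | 82.9% |
| 0.7 | 2.86 | 90.3% |

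**4. Slope against the adjusted week-12 difference.** Power at the stated 63 per group (normal approximation), true effect linear and reaching 1.7 at week 12:

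| ρ | Week-12, adjusted | Slope, compound symmetry | Slope, AR(1) |
|---|---|---|---|
| 0.3 | 70.6% | 56.6% | 52.3% |
| 0.5 | 78.7% | 71.0% | 66.5% |
| 0.7 | 91.6% | 90.1% | 86.9% |
| 0.8 | 97.8% | 97.8% | 96.5% |

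The unadjusted week-12 difference has 66.5% here. Even when linearity holds, the slope never beats the adjusted contrast in these cases. It ties at ρ = 0.8 under compound symmetry.

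**5. What the slope implies for week 12 when the effect is not linear.** Code the visits 0, 1, 2, 3. The least-squares slope uses weights −1.5, −0.5, 0.5, 1.5 divided by 5, and the implied week-12 difference is 3 × slope. On complete data a random-intercept model gives the same value.

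| Effect at weeks 0, 4, 8, 12 | True week 12 | Implied by slope |
|---|---|---|
| 0, 1.7, 1.7, 1.7 (full from week 4) | 1.7 | 1.53 |
| 0, 0.85, 1.7, 1.7 (plateau from week 8) | 1.7 | 1.785 |
| 0, 0.85, 1.7, 0.85 (halves after week 8) | 0.85 | 1.02 |
| 0, 0.85, 1.7, 0 (vanishes) | 0 | 0.255 |

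Example, third row: (−0.5 × 0.85 + 0.5 × 1.7 + 1.5 × 0.85) / 5 = 0.34, and 3 × 0.34 = 1.02.

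Under AR(1) errors with ρ = 0.5 the same four paths give 1.69, 1.71, 0.86 and 0.02, so the distortion nearly disappears. The answer therefore depends on a covariance structure that the article does not state.

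**The case against.** The strongest reply is that the slope model has an evident role. Childhood adversity and a severity term come close to the predictor hypotheses under the secondary objectives (which refer to acute severity, whereas the model uses Long COVID severity). On that reading the mean difference serves the trial comparison and the regression serves prediction. This is reasonable, but the article does not say so. The model lists group first among its effects, takes the primary outcome as its response, and sits in the paragraph on the primary analysis.

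A second reply is that covariate lists belong in an analysis plan that is not shown. That stands as far as silence goes: the article never says the mean difference is unadjusted, and baseline WHODAS enters the slope model as the first of its four time points. What remains is the undesignated primary analysis and a named model that includes other prognostic terms but not the strata.

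Three stronger readings are tempting and not supported:

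- *No randomised comparison is stated.* Intention-to-treat on all randomised participants is stated, and the objective fixes 3 months. Only the sentence joining them is missing.
- *Treatment received competes as a primary estimand.* It is introduced as additional and is not defined, so how non-users would be classified is unknown. Grouping by engagement would not be a randomised comparison, which matters for its label only.
- *Both strata are called main determinants of outcome.* Only symptom duration is.

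On size, the low starting power comes mainly from the sample-size arithmetic and not from lack of adjustment. The non-linear paths are illustrations, with distortions of at most about 0.26 points.

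**Conclusion.** The point holds in this form: the primary analysis is not designated, and the one model specified does not match the 3-month objective, the sample-size basis or the stratified design. The ambiguity itself is plain from the text and rests on no assumption.

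The sizes are conditional. Baseline adjustment adds about 4 to 26 percentage points of power over an unadjusted week-12 comparison (68.5% to 90.3% against 64.4%), for an assumed correlation of 0.3 to 0.7. The article does not commit to that unadjusted comparator, so this is the gain available and not a loss that the plan has fixed. The slope's distortion is modest, depends on the scenario and is close to nil under AR(1) errors. The benefit of including the strata cannot be computed from the article.

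This should be corrected, but it does not show that the trial lacks a valid randomised comparison.

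**What to change.** State one primary analysis: in all randomised participants as allocated, the ECM+ minus HC difference in WHODAS at week 12 with its 95% confidence interval, adjusted for baseline WHODAS, sex and symptom-duration stratum. Either ANCOVA at week 12 or a repeated-measures model for weeks 4, 8 and 12 will do. The latter needs categorical visit and an arm-by-visit term, with the week-12 contrast named as decisive.

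Label the linear-slope model as secondary, serving the predictor objective, and the treatment-received analysis as supplementary, with a definition of treatment received. A complier-average analysis using the NexJ usage data is an option. It needs the assumption that allocation acts only through platform use, which is hard to defend in an open-label trial.

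The cost is wording in the protocol and analysis plan, settled before outcomes are examined by group. Baseline WHODAS and both strata are already collected. Adjustment does not replace correcting the sample size: for 1.7 points, 63 per group analysed reaches 80% power only if the correlation is about 0.52 or higher (√(1 − 63/86.9) = 0.52).
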